### *Patient-related and psychosocial factors*

Since adolescence is a period of transition from being a child to assuming adult identity, most often the responsibility of care is moved from caretakers to ALWHAs. This is the point when individual-related factors mostly become prominent in influencing health-seeking behaviors. The interaction of ALWHs with the social environment impacts their psychological and physical states which might also influence adherence-related behaviors. This assertion takes into consideration that “the mind is the doorway through which individuals experience environmental events”. Thus, social factors such as losing parents, disclosure of status, victimization and discrimination coupled with effects of developmental changes such as attenuated risk-taking, abstract reasoning and desire for immediate gratification, affect cognition and also evoke psychopathological experiences such as stress, anxiety, depression, and stigma which are proximal barriers to medication adherence.

Experiencing depression is very common among ALWHA, and it's always associated with mortalities. According to WHO, ‘depression is a mental disorder characterized by persistent sadness and a lack of interest or pleasure in previously rewarding or enjoyable activities. It can disturb sleep, loss of appetite and cause tiredness and poor concentration. Depression is caused by the interplay of social, psychological and biological factors. Higher levels of depression have been identified among ALWHA in Uganda; in a cross-sectional study conducted in Western Uganda, the prevalence of depressive symptoms among adolescents (10-19) was high (46%) and highest among older adolescents (62.3%). The most reported depressive symptoms are: “feeling unhappy”, “feeling like crying” and “lack of appetite”. Similarly, another study carried out in rural Uganda found higher levels of depression among ALWHA. Participants reported experiencing greater psychological pain due to resentment and feeling sad, this often results in self-isolation and sometimes the development of suicidal thoughts like ‘taking rat poison’, ‘throwing self in the lake’ and ‘cutting the neck’. Evidence of experiences of depression among ALWHA is enormous.

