*Short health anxiety inventory (SHAI-Salkovskis et.al, 2002)*. This is an 18-item measure of health-related anxiety independent of physical health status. It has commonly been used to assess health anxiety among adolescents and has good psychometric properties. The items of SHAI assess worry about health, awareness of body sensations or changes, and feared consequences of having an illness. Its overall reliability co-efficient is  $\alpha=.93$ , then fear of illness (items 1-14) have  $\alpha=.84$  and negative consequences of an illness (items 15-18)  $\alpha=.67$ . All items show corrected item-total correlations  $\geq .30$  which is considered acceptable. Responses from the instrument are scored on a 4-point Likert scale, where 0 =no symptom, 1 =mild symptom, 2 =severe symptoms and 3 =very severe symptoms. If more than one statement is selected, the higher-scoring statement is considered. The obtained total score ranges between 0-54 with higher scores representing higher anxiety. A cut-off of 40.5 (total score) distinguishes between non-clinical to severe anxiety.

*Internalized AIDS-related stigma scale (IARSS-Kalichman 2009)*. This is a 6-item scale reflecting self-defeating beliefs and negative perceptions of people living with HIV/AIDS. This instrument has been used and validated in a Ugandan context. Items of the IARSS are assessed with a binary response of YES/NO and a total scale score is computed as the sum of all the 6-items. Higher scores indicate higher levels of internalized HIV/AIDS-related stigma. IARSS has demonstrated acceptable internal consistency ( $\alpha=.75$ ) and time stability when used in Uganda. Construct validity shows that the scale correlates with related constructs such as depression and mental health-related quality of life.

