| To examine the impact of ACT-DNA-v on reducing proximal psychosocial barriers to medication adherence (depression, anxiety and stigma) among ALWHA | Depression
Anxiety
Internalized stigma            | ALWHA | Qualitative surveys using standardized data collection instruments.
* Reynolds Adolescents depression scale (RADS-2)
* Social anxiety scale for adolescents-short form (SA-A-SF).
* Internalized AIDS-related stigma scale (IARSS-6). | 
Analysis
We shall run a T-test, linear regression, and Fisher's exact and Chi-square tests respectively to obtain mean differences between groups.
 
Outcomes we hypothesize that;
*The average means score of ALWHA in the intervention arm should be in the mild depression range of the BDI-ii (14-19) at post-intervention and follow-up, adjusting for baseline compared to the mean score of ALWHA in the control group.
* The average mean score of ALWHA in the intervention arm should be below the cutoff score of 40.5 as measured by the SHAI at post-intervention and follow-up.
* After dichotomizing the IARSS-6 at median value (0-2 & 3-6), average mean scores of participants in the intervention arm should fall in category1 (0-2) at post-intervention and follow-up.
 |

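### Table 2 states the expected primary results as fixed ranges for the intervention-arm mean, which conflicts with the protocol's between-arm hypothesis and leaves the criterion for success unclear

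*Protocol*

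**What the plan says.** The Outcome measures section names depression, anxiety and internalized stigma as the primary clinical outcomes. In Table 2, the row on the impact of the intervention gives one expected result for each:

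- **Depression (BDI-II):** "The average means score of ALWHA in the intervention arm should be in the mild depression range of the BDI-ii (14-19) at post-intervention", and likewise at follow-up. The sentence goes on: "adjusting for baseline compared to the mean score of ALWHA in the control group".
- **Anxiety (SHAI):** the intervention-arm mean "should be below the cutoff score of 40.5 as measured by the SHAI at post-intervention and follow-up". No control arm is mentioned.
- **Stigma (IARSS):** "After dichotomizing the IARSS-6 at median value", with the categories already given as 0-2 and 3-6, "average mean scores of participants in the intervention arm should fall in category1 (0-2) at post-intervention and follow-up". No control arm is mentioned.

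The Analysis line of the same cell lists a T-test, linear regression, Fisher's exact and Chi-square tests as the means of obtaining mean differences between groups. The Hypothesis section predicts a significant reduction in the intervention group relative to control at post-intervention. The Statistical analysis section says that individuals will be compared on the outcomes in Table 2 by intention to treat.

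**The concern.** Whether one arm's mean lies inside a fixed range is a different question from whether the arms differ, and the two can have opposite answers. A range that the control arm would also satisfy says nothing about treatment. A range with a lower edge on a scale where lower is better counts a sufficiently good result as a miss. Because the Statistical analysis section points back to Table 2 for the outcomes, its wording matters. As it stands, a report could claim that the anxiety and stigma hypotheses were met without any difference between arms, or that the depression hypothesis failed despite a large benefit.

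**Working it through.** **Number analysed per arm.** The Sample size section uses a difference of 4.09, SD 5.13, and Z values 1.96 and 0.84:

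2 × (1.96 + 0.84)² × 5.13² / 4.09² = 24.7

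The protocol prints 25.1 and takes 26. Then 26 × 2.0 (design effect) = 52; 52 / 0.90 = 57.8, so 58 per arm and 116 in total. The final figure reproduces, and the small difference at the first step does not affect this point. I use 52 analysed per arm. Applying the protocol's own design effect gives an effective 52 / 2.0 = 26.

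**SHAI.** Study instruments gives 18 items scored 0-3, where 2 is labelled severe and 3 very severe, and: "The obtained total score ranges between 0-54 with higher scores representing higher anxiety". The target of 40.5 is 40.5 / 54 = 75% of the maximum, or 40.5 / 18 = 2.25 per item, above the severe label on average. The Inclusion Criteria cover age, HIV status, care attendance, treatment line, language and consent; none sets a minimum symptom score. Suppose both arms have the same true mean, so there is no effect (means and SD assumed). Then P(observed mean < 40.5) = Φ((40.5 − mean)/SE), with SD 10:

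| True mean in both arms | n = 52, SE = 10/√52 = 1.39 | Effective n = 26, SE = 10/√26 = 1.96 |
|---|---|---|
| 38 | 0.96 | 0.90 |
| 35 | 1.00 | 1.00 |

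The target is met almost surely with no effect unless the true mean is close to 40.5.

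**IARSS.** The scale is a sum of six yes/no items, range 0-6. With no effect and an assumed true mean of 1.5 in both arms, P(observed mean ≤ 2) = Φ(0.5/SE). For SD 1.5 to 2 this is 0.99 to 0.96 with n = 52, and 0.95 to 0.90 with effective n = 26. The cut is called a median, but its value is fixed before any data exist, and a mean is then assigned to a category.

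**BDI-II.** Study instruments gives 0-13 minimal, 14-19 mild, 20-28 moderate and 29-63 severe. A mean of 10 is better than a mean of 18, yet 18 is inside the target and 10 is not. For an illustration, P(14 < observed mean < 19) = Φ((19 − m)/SE) − Φ((14 − m)/SE). The true means and SD are assumed, because the protocol gives no BDI-II SD (5.13 is for RADS-2):

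| True intervention mean m | SD 10, n = 52 | SD 10, effective n = 26 | SD 8 to 12, n = 52 |
|---|---|---|---|
| 12 (better) | Φ(5.05) − Φ(1.44) = 0.07 | Φ(3.57) − Φ(1.02) = 0.15 | 0.04 to 0.11 |
| 16 (worse) | Φ(2.16) − Φ(−1.44) = 0.91 | Φ(1.53) − Φ(−1.02) = 0.78 | 0.96 to 0.85 |

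If control is 20 and intervention 12 (an 8-point benefit, SD 10), the range is met about 7% of the time with n = 52, while a two-sided 5% between-group test has 98% power: Φ(8/(10√(2/52)) − 1.96). With effective n = 26 the figures are 15% and 82%.

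**Tests listed.** Fisher's exact and Chi-square tests compare proportions and give no mean difference. A T-test gives an unadjusted difference. Linear regression gives a mean difference and can carry the baseline adjustment that the BDI-II sentence asks for.

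**The case against.** The best defence is that the ranges are introduced as what the investigators hypothesise, not as a decision rule. The rest of the plan is comparative: the Hypothesis section, the Abstract's methods, a sample size built on a between-arm difference, the Analysis line in the same cell, and the intention-to-treat comparison. Linear regression and baseline adjustment are both already named, and fuller model detail may properly sit in a statistical analysis plan. This stands. A reader might infer that the trial will declare success on these ranges alone, but no section says so.

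Two further inferences also go beyond the text. One is that the BDI-II target can be met with no effect. Its sentence refers to the control arm, and if that clause is an added condition, the inference fails. Success without effect is therefore firm for SHAI and IARSS only; missing the target despite a real benefit holds for BDI-II on either reading. The other is that participants will certainly start with low scores. The literature review reports depressive symptoms in 62.3% of older adolescents in one Ugandan study, with no BDI-II mean, and the protocol has no SHAI baseline data. Meeting 40.5 before treatment is likely from the per-item arithmetic, not established.

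Fisher's exact and Chi-square tests would suit a dichotomised IARSS. That defends listing them for a proportion, not as a source of mean differences.

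**Conclusion.** The point holds as a conflict within the protocol. The three Table 2 targets do not express the between-arm hypothesis, and the document does not say which of the two decides. For SHAI and IARSS the target has no control reference and can be met with no effect. For BDI-II the comparison with control has no direction or margin, and the lower edge of 14 excludes a better result.

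The size of the problem is illustrative: at SD 10, about 7% against 91% for true BDI-II means of 12 and 16, or about 15% against 78% with the design effect of 2.0. These figures rest on assumed means and SD and a normal approximation for the arm mean. The ordering, with the worse mean meeting the target far more often, is the same at every SD tried. The logical defect does not depend on any of these figures.

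**What to change.** In Table 2, replace the three threshold statements with one quantity per scale: the baseline-adjusted between-arm difference in mean score at post-intervention, with its 95% CI, from the linear regression already listed, with arm, baseline score and site as terms. Make follow-up secondary. Analyse the IARSS as its 0-6 sum. Keep the BDI-II, SHAI and IARSS bands only as descriptive percentages in each arm. Drop Fisher's exact and Chi-square tests for the scale scores.

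The cost is a change of wording in Table 2. The Sub-study design section already provides for baseline depression, anxiety and stigma data, so no visit, instrument or sample-size change is needed.

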### Methods

Sequential multi-methods design will be used, commencing with a formative phase where ACT-DNA-v will be adapted to fit the specific needs of users and providers in Kampala and using semi-structured interviews, explore the acceptability of ACT-DNA-v among users and providers, as well as implementation related factors. This phase will be followed by measuring the feasibility and effectiveness of the adapted ACT-DNA-v in improving mental health outcomes among ALWHA with a randomized control trial (RCT). The trial will involve quantitative surveys at baseline, post-intervention and follow-up, testing the effects of the intervention on process and clinical outcomes among ALWHA. Thematic analysis that involves coding, analysis and interpretation of findings utilizing qualitative data analysis software (QDA) will be used for the qualitative study, while T-test, Fisher's exact, regression, Chi-square tests and analysis of variance (ANOVA) respectively will be used in the quantitative phase to ascertain average mean differences between the two study groups on the outcome parameters of depression symptoms, anxiety, and stigma at pre-post intervention and psychological flexibility at follow-up.

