##### *Inclusion Criteria:*

Participant should be 15-19 years of age, diagnosed HIV positive, attending care at Kisenyi Kitebi health center for the last 6 months, on first or second line of treatment, can speak/understand

Luganda or English and willing to provide informed consent/assent. All records will be confirmed via clinic medical charts.

*Exclusion criteria:*

A participant will not be eligible to be part of the study if he/she plans to move out of the catchment area within six months, or if he/she is participating in another study related to HIV and care improvement.

*Sampling for sub-study two*

*Sample size*

The following assumptions are considered for determining the appropriate sample size for the quantitative study.

Assumptions:

$$N = 2 \frac{[Z\alpha + Z\beta]^2 S^2}{(\mu_1 - \mu_2)^2}$$

where:

$Z\alpha$  is standard normal value corresponding to level of significance

$Z\beta$  is standard normal value corresponding to power of the study

$\alpha$ =acceptable type 1 error

$\beta$ = type II error

$\mu_1$  is mean in control group and  $\mu_2$  is mean intervention

$\mu_1 - \mu_2$  =effect size (minimum meaningful difference between the means in the control and intervention groups)

$S$ =standard deviation of the outcome in the control group

$N$  is the sample size per group

$Z\alpha = 1.96$ ,  $Z\beta = 0.84$ ,  $\alpha = 0.05$  in 2 tails,  $\beta = 0.20$  (at 80% power).

Considering a study evaluating effectiveness of Acceptance and Commitment Therapy (ACT) on reducing the depressive symptomatology among Swedish and Australian adolescents (Livheim et.al, 2015), the difference in means of the post treatment RADS2 scores between the ACT arm and control arm was 4.09 while the standard deviation in the control arm was 5.13.

Substituting into the formula,

$$N = (2(1.96 + 0.84)^2 \times 5.13^2) / (4.09^2)$$

$$N = 25.1$$

N=26 participants in each group

If we consider a possible clustering in any of the two sites and a design effect of 2.0, the new minimum sample size is  $26 \times (2) = 52$ . If we consider a 10% loss to follow-up, the revised sample size will become  $(52 \times (1 / (1 - 0.10))) = 58$  participants. We, therefore, aim to recruit, **a total of 116 participants** at 80% power of detecting a mean difference of 4.09 or more in the intervention.

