#### Outcome measures.

Measured clinical primary outcomes will include Experiences of depression, anxiety and internalized stigma. Then process outcomes will include; Psychological flexibility (cognitive fusion and experiential avoidance) to test the mechanism of change and secondary outcomes will be; self-reported adherence and viral load (obtained from clinical charts).

Table 2; Showing study measures, analysis and outcomes.

| Objective                                                             | Variables                                                                                                                                      | Informant | Measures                                                                                                                                                                                                                                                                                                                                                                                                                                                      | Analysis & Outcomes                                                                                                                                                                                                                                                                                                                                                                             |

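### Table 2 dichotomizes the internalized stigma score, a primary outcome, while describing mean scores; no test is fixed for stigma, the sample size gives it no power in either form, and testing the split would lose information

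*Protocol*

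**What the plan says.** The protocol's Outcome measures section makes stigma primary: "Measured clinical primary outcomes will include Experiences of depression, anxiety and internalized stigma". Study instruments scores the IARSS from six yes/no items, and "a total scale score is computed as the sum of all the 6-items", so the score runs from 0 to 6.

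Table 2, in the row for depression, anxiety and stigma, sets the stigma expectation "After dichotomizing the IARSS-6 at median value (0-2 & 3-6"), and continues that "average mean scores of participants in the intervention arm should fall in category1 (0-2) at post-intervention and follow-up". The analysis entry for the whole row is "We shall run a T-test, linear regression, and Fisher's exact and Chi-square tests respectively to obtain mean differences between groups". The abstract's Methods paragraph says the tests are used "to ascertain average mean differences between the two study groups on the outcome parameters of depression symptoms, anxiety, and stigma".

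The sample-size section uses the two-means formula "in 2 tails, $\beta = 0.20$ (at 80% power"), with a difference of 4.09 and a standard deviation of 5.13 taken from a trial in Swedish and Australian adolescents that used a depression scale. Its power statement is "at 80% power of detecting a mean difference of 4.09 or more in the intervention". The Statistical analysis section then says the arms will be compared on the outcomes listed in Table 2.

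**The concern.** Table 2 describes two different analyses of one primary outcome. A score that has been split into two categories yields a proportion in each arm, not a 0-6 mean that can lie in a band. A mean on the 0-6 scale needs no split. Because the Statistical analysis section sends the reader to Table 2 for the outcomes, the contradiction carries into the main comparison.

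If an analyst follows the word about dichotomizing, scores of 0 and 2 count as equal, so do scores of 3 and 6, and a change of one answer from 3 to 2 counts as full success. That costs power relative to the sum score already defined. The study hypothesis claims a significant reduction in depression, anxiety and stigma together, so a null stigma result caused by the split could be read as an absence of effect. Leaving both forms open also allows the choice to be made after the data are seen.

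**Working it through.** **Step 1. The protocol's own sample size.** Inputs from the sample-size section: difference 4.09, SD 5.13, z-values 1.96 and 0.84, design effect 2.0, loss 10%.

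- N per group = 2 × (1.96 + 0.84)² × 5.13² / 4.09² = 24.7. The protocol prints 25.1 and uses 26, which is close enough to make no difference here.
- 26 × 2 = 52; 52 / 0.90 = 57.8, so 58; 2 × 58 = 116. The stated total reproduces.
- Every input concerns a depression mean. No stigma effect, stigma SD or proportion enters.

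**Step 2. Power for a mean.** Standardized effect d = 4.09 / 5.13 = 0.797. The planned 52 evaluable per arm count as 52 / 2 = 26 under the protocol's design effect. A two-sided 5% t-test (noncentral t) has 80.5% power at 26 per arm and 98.1% at 52 per arm.

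**Step 3. Power if the split is tested.** The documents give neither a stigma effect nor the share of participants scoring 0-2. Assumptions: the same d = 0.797 applies on an underlying normal score, and the control proportion in the low category, p_C, is 0.30 to 0.70. Table 2 calls the cut a median, which suggests 0.50, but the cut-point is fixed in advance, so the actual share could differ.

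Intervention proportion: p_I = Φ(Φ⁻¹(p_C) + 0.797). At p_C = 0.50 this is Φ(0.797) = 0.787. Power by exact enumeration, two-sided 5%:

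| p_C | p_I | Chi-square, 26 per arm | Fisher, 26 per arm | Chi-square, 52 per arm | Fisher, 52 per arm |
|---|---|---|---|---|---|
| 0.30 | 0.608 | 60.4% | 50.5% | 90.9% | 87.2% |
| 0.50 | 0.787 | 61.1% | 49.4% | 88.2% | 83.3% |
| 0.70 | 0.907 | 50.2% | 35.2% | 78.1% | 70.6% |
| Mean (t-test) | | 80.5% | | 98.1% | |

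The t-test row gives one figure for each sample size.

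**Step 4. The same loss as sample size.** At 0.50 versus 0.787, the usual two-proportions formula needs 43 per arm for 80% power, against 25 for the mean: 43 / 25 = 1.72, about 70% more. With the protocol's inflation this is 2 × 43 / 0.90 = 95.6, so 96 per arm and 192 in total, against 116.

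**The case against.** A reader might infer that the protocol plans a test of proportions for stigma, since Fisher's exact and chi-square tests appear in that row and only the IARSS is split there. The text does not support that as a fact. All the listed tests are said to give mean differences, the abstract names mean differences for stigma, and the next row of Table 2 repeats the same test list for the AFQ-Y8, which is not split. The list is generic wording and assigns no test to stigma.

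The sentence also stands under the hypothesized outcomes, not under the analysis, and parallels the BDI-II and SHAI entries, each of which sets a target band for the intervention-arm mean. The 0-2 category may be no more than such a band, in which case nothing is lost. This reading is possible, but it does not explain why the score is said to be dichotomized, and the contradiction remains.

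On size, the shortfall against 80% depends largely on the design effect of 2.0. Randomization is individual and 1:1, and clustering by site is only raised as a possibility. The normal-score model is also not the only one. For simulated 0-6 scores (beta-binomial, assumed control means 2.1 to 3.3, same standardized effect), power at 26 per arm is about 65-78% by chi-square and 55-65% by Fisher, against 82-93% by t-test. At 52 per arm it is 94-97% and 91-95%, against 98-99.8%. The split loses power in each of these cases too, but less.

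A statistical analysis plan could name the test for each outcome. It would still have to depart from one half of Table 2's sentence.

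**Conclusion.** The point holds as a contradiction in how a primary outcome is defined, with a conditional loss of power. Table 2 splits the IARSS-6 and in the same sentence treats it as a mean, no test is tied to stigma, and the sample size gives stigma no power in either form.

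If the split is tested, power under the normal-score assumption is about 50-61% (chi-square) or 35-50% (Fisher) on the protocol's own design effect, against 80% for means. Without a design effect it is about 78-91% or 71-87%, against 98%. These ranges rest on three assumptions: a stigma effect equal to the depression effect of 0.797, a normal underlying score, and 30-70% of controls scoring 0-2.

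It would go too far to say that stigma falls well below a stated 80% power. The 80% is stated only for the depression mean difference, and without clustering most of the scenarios stay above 80%. What is common to every case computed is that, for the same effect, the split has less power than the sum score.

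**What to change.** In Table 2, delete the dichotomization of the IARSS-6 for the primary comparison. State instead that stigma is the 0-6 sum score defined under Study instruments, compared between arms as a mean difference at post-intervention by the linear regression already listed, adjusted for the baseline IARSS score. If the scores are strongly skewed, use robust or bootstrap standard errors. Keep the proportions scoring 0-2 and 3-6 as a descriptive summary only.

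This is a wording change. It needs no new data, visits or participants, and it agrees with the abstract and the instrument section. The small downside is that the category is no longer the tested result, although it can still be tabulated.

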### Study instruments

*Beck's Depression Inventory ii (BDI ii, Beck et.al, 2006)*. BDI-ii is a 21 item self-report rating inventory widely used to measure the presence and degree of depression among adolescents and adults. The BDI-ii includes both cognitive and somatic symptoms of depression. It has a high test retest reliability  $r=.93$  and high internal consistency  $\alpha=.91$ . In scoring the BDI-ii, each of the 21 items is summed up to give a single score. Each item has a 4-point scale ranging from 0-3, except items 16&18 that have 7 options indicating either an increase or decrease of appetite and sleep. The total score in the range of 0-13 =minimal range, 14-19=mild, 20-28=moderate and 29-63= severe.. The cut-off guidelines for BDI-ii are adjusted basing on characteristics of the sample.

*Avoidance and Fusion Questionnaire for youths (AFQ-Y8; Greco et.al, 2008)*. This is a measure of psychological inflexibility among children and adolescents. It is an 8-item instrument where participants rate their level of agreement with statements targeting cognitive fusion and experiential avoidance such as "my thoughts and feelings mess up my life". AFQ-Y8 is scored on a 5-point Likert scale made up of a single factor. Scores range from 0-24, with higher scores indicating higher levels of psychological inflexibility. The instrument has shown excellent internal

consistency ( $\alpha=.90$ , and test-retest validity  $r=.80$ ). It also correlates well with measures of anxiety, depression and anger and is better recommended for use among adolescents.

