| To measure the effectiveness of a mindfulness-based intervention (ACT-DNA-v) on psychological flexibility among ALWHA in Kampala.                  | Process variable:
*Psychological flexibility. | ALWHA | Qualitative surveys using standardized self-administered instruments

* Avoidance and Fusion Questionnaire for youths (AFQ-Y8).                                                                                                          | 
Analysis
We shall run a T-test, linear regression, and Fisher's exact and Chi-square tests respectively to obtain mean differences between groups.
 
Outcomes
*The average mean scores of participants in the intervention group will be above the cut-off score on psychological inflexibility using the AFQ-8 at post-intervention and follow-up adjusting for baseline scores.
                                                                                                                                                                                                                                                                                                                                                                                                                       |

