### Statistical analysis

All participant data will be entered into Epidata Manager or RedCap software to facilitate electronic capture of the data. After data cleaning using programmed logic checks and assessment for logic accuracy and consistence, the final database will be locked. The data will be analyzed using the Statistical Package for Social Scientists (SPSS) version 26.0. A table of baseline

characteristics will be drawn with continuous and categorical variables between the intervention and control arm compared using T-test, linear regression, Fisher's exact and Chi-Square tests respectively. A p-value of less than will be considered statistically significant. The individuals will be compared on the outcomes shown in table 2 above of this sub-study following an Intention to treat analysis (ITT) approach. The ITT population will be defined as all randomized patients with data for the outcomes. However, per protocol analysis will also be carried out and results compared with the ITT. The results will be reported following the CONSORT 2010 guidelines.

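### Table 2 states the expected AFQ-Y8 result on the unfavourable side of an unspecified cut-off, and the scale's item count, response options and total range do not agree

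*Protocol*

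**What the plan says.** The Outcome measures section makes psychological flexibility the process outcome, included to test the mechanism of change. The AFQ-Y8 is its only instrument in Table 2.

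- **Construct (Study instruments):** "This is a measure of psychological inflexibility among children and adolescents".
- **Items and response format (Study instruments):** "It is an 8-item instrument where participants rate their level of agreement with statements", and "AFQ-Y8 is scored on a 5-point Likert scale made up of a single factor".
- **Range and direction (Study instruments):** "Scores range from 0-24, with higher scores indicating higher levels of psychological inflexibility".
- **Expected result (Table 2, process-variable row):** "The average mean scores of participants in the intervention group will be above the cut-off score on psychological inflexibility using the AFQ-8". The row applies this at post-intervention and follow-up, with adjustment for baseline.
- **Aim (Study intervention):** the sessions are meant to improve psychological flexibility.
- **Use of Table 2 (Statistical analysis):** the arms are to be compared on the outcomes in that table. The same section says of data handling: "After data cleaning using programmed logic checks and assessment for logic accuracy and consistence, the final database will be locked".

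No numerical AFQ-Y8 cut-off appears anywhere in the protocol.

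**The concern.** On a scale where a high score is bad, the expected benefit should be a low score. The AFQ-Y8 row puts the treated arm on the high side. Because the Statistical analysis section points to Table 2 for the comparisons, that row is the protocol's pre-stated reading of the mechanism outcome. A criterion with the wrong direction and no threshold leaves the meaning of success open until the data are seen. That matters more because the trial is open-label.

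The description of the scale also fails a simple check: the item count, the number of response options and the total range cannot all be correct. Anyone scoring the questionnaire, or setting limits for its total, has to guess which one to believe.

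**Working it through.** **1. Direction.** The entries side by side, all from the protocol:

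| Scale | What a high score means | Expected result in the intervention arm (Table 2) |
|---|---|---|
| SHAI (anxiety) | more anxiety | below 40.5 |
| IARSS (stigma) | more stigma | lower category, 0-2 of 0-6 |
| AFQ-Y8 (process) | more inflexibility | above a cut-off, value not given |

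The SHAI and IARSS rows place the expected result on the low side. Only the AFQ-Y8 row places it on the high side. The protocol describes no reverse scoring, and the row itself names the cut-off as one on inflexibility, so it cannot be read as referring to a flexibility score.

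**2. Total range.** The assumption is that the total is the plain sum of items coded in consecutive whole numbers; the protocol describes no rescaling. Then:

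minimum = items x lowest code; maximum = items x highest code.

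The rule reproduces the upper limits of the other scales in the protocol:

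- BDI-II: 21 x 3 = 63, as stated.
- SHAI: 18 x 3 = 54, as stated.
- IARSS: 6 x 1 = 6, as used in the 0-2 and 3-6 split.

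Applied to the AFQ-Y8 with 8 items:

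| Response options | Coding | Total range |
|---|---|---|
| 5 | 0-4 | 0-32 |
| 5 | 1-5 | 8-40 |
| 4 | 0-3 | 0-24 |
| 4 | 1-4 | 8-32 |

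The stated 0-24 is not reproduced by either five-option coding. Working back, 24 / 8 = 3 as the highest item code, which means four options starting from 0. Five options coded 0-4 would reach 24 only with 24 / 4 = 6 items.

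**3. What a 0-24 limit would exclude.** This depends on the coding. If items have five options coded 0-4, there are 33 possible totals (0 to 32), and 8 of them (25 to 32) exceed 24. If items have four options coded 0-3, none do.

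**The case against.** The strongest reply is that the faulty sentence is a statement of expectation, not an estimator or a test. The analysis named in the same row is a t-test and regression for between-group mean differences. It gives the same signed estimate whatever the sentence predicts, and the Study instruments section tells the analyst how to read the sign. The AFQ-Y8 is also not among the primary outcomes (depression, anxiety and internalized stigma). Neither the formal hypothesis nor the sample size uses it. The cut-off value might be supplied in an analysis plan that is not shown.

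Most of this stands, and it rules out three stronger readings that a reader might infer:

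- **That the trial's mechanism conclusion would be reversed, with a worsening confirming it and an improvement refuting it.** The criterion concerns the level of one arm against a cut-off, not change. An arm can improve and stay above a cut-off, or worsen and stay below it. With no value given, the criterion cannot return a verdict in either direction.
- **That 0-32 is the true range.** The protocol's figures fit equally well with the number of response options being the slip and 0-24 being right.
- **That valid high scores would be rejected.** The Statistical analysis section mentions logic checks but does not link them to the AFQ-Y8 total or to 0-24.

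The reply does not remove the contradictions themselves. An analysis plan could add a cut-off value, but the protocol's stated direction would still conflict with its own scoring.

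**Conclusion.** The point holds as two errors in the protocol's text.

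First, the expected AFQ-Y8 result is stated in the wrong direction relative to the scale's own scoring and the aim of the intervention. It also refers to a cut-off the protocol does not define. As written, the criterion is mis-signed and cannot be applied. This conclusion rests only on the protocol's wording.

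Second, eight items, five response options and a 0-24 total are incompatible, assuming a simple sum of whole-number codes. Which element is wrong cannot be settled from the document.

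The reach is limited. The errors affect the pre-stated criterion for the process outcome and its interpretation; the between-arm test, the primary outcomes and the sample size are untouched. Harm through data checks would arise only if a check were programmed at 0-24 while the items in use have five options. In that case, with 0-4 coding, totals of 25 to 32 would be queried, and these belong to the most inflexible participants.

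**What to change.** **Criterion (Table 2, process-variable row).** Replace it with a lower mean AFQ-Y8 in the intervention arm than in control at post-intervention and follow-up, adjusted for baseline. The row already carries the baseline adjustment and both time points. If a cut-off is to be kept, state its value and change above to below.

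**Scale description (Study instruments).** Check the AFQ-Y8 version in use, then make the number of response options, the item coding and the total range agree. Set any data-entry or cleaning limit for the AFQ-Y8 to match.

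The cost is a sentence in Table 2, a phrase in Study instruments and, if one exists, one data-check limit. No change to the design, sample size or data collection follows from this correction, provided the questionnaire in use is the intended version.
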